## Abstract

**Background:**

Hemodynamic monitoring is very important in critically ill patients with shock or acute respiratory distress syndrome(ARDS). The PiCCO (Pulse index Contour Continuous Cardiac Output, Pulsion Medical Systems, Germany) system has been developed and used in critical care settings for several years. However, its impact on clinical outcomes remains unknown.

**Methods/design:**

The study is a randomized controlled multi-center trial. A total of 708 patients with ARDS, septic shock or both will be included from January 2012 to January 2014. Subjects will be randomized to receive PiCCO monitoring or not. Our primary end point is 30-day mortality, and secondary outcome measures include ICU length of stay, days on mechanical ventilation, days of vasoactive agent support, ICU-free survival days during a 30-day period, mechanical-ventilation-free survival days during a 30-day period, and maximum SOFA score during the first 7 days.

**Discussion:**

We investigate whether the use of PiCCO monitoring will improve patient outcomes in critically ill patients with ARDS or septic shock. This will provide additional data on hemodynamic monitoring and help clinicians to make decisions on the use of PiCCO.

**Trial registration:**

http://www.clinicaltrials.gov NCT01526382

## Background

Hemodynamic monitoring and the associated fluid therapy are of critical importance in the management of critically ill patients. The optimization of fluid status remains a challenge in critical care settings because fluid overload will lead to organ edema and an ensuing increase in mortality
[1,2], whereas inadequate circulating volume will result in insufficient perfusion pressure and oxygen delivery. Therefore, monitoring the fluid status of critically ill patients is very important. Recent decades have witnessed rapid advances in fluid monitoring techniques. Pulmonary artery catheters have been widely used for more than five decades, but unfortunately their usefulness in improving patient outcomes seems disappointing
[3]. The PiCCO system (Pulse index Contour Continuous Cardiac Output, Pulsion Medical Systems, Germany) incorporates a transpulmonary thermodilution technique (TPTD) and continuous pulse contour analysis. It is a minimally invasive technique, which gives beat-by-beat monitoring of cardiac output, and can provide accurate information on volume status and pulmonary edema. Furthermore, the PiCCO monitor is an ‘all-inclusive’ device, which provides a full picture of a patient’s hemodynamic status, including vascular tone, preload, and cardiac function
[4]. However, clinical studies investigating the usefulness of the PiCCO system have mainly focused on intermediate physiological parameters, such as fluid responsiveness, oxygenation and pulmonary edema,
[5,6], and only a few studies have investigated clinical outcomes of patients managed using a PiCCO monitor
[7,8]. Although these studies have promising results, the link between its use and clinical outcomes (for example mortality, length of stay in an ICU, duration of mechanical ventilation) is largely unknown.

Patients with acute respiratory distress syndrome (ARDS) are characterized by increased pulmonary extravascular lung water (EVLW), and may potentially benefit from EVLW monitoring. Simmons *et al*.
[9] noticed that a more negative fluid balance in ARDS patients was associated with improved survival. More recently, numerous studies have demonstrated that elevated EVLW is associated with an increased mortality rate
[10,11]. A recent meta-analysis by our group also supports this notion
[12]. Thus, management algorithms aiming to optimize the extravascular lung water index (EVLWI) are assumed to be beneficial to this group of patients. The other disease entity that is commonly encountered in ICUs is septic shock. This group of patients usually receives infusions of large amounts of fluid during theinitial period to maintain an adequate perfusion pressure. Early goal-directed therapy (EGDT), as proposed by Rivers, is a clinically useful bundle to guide fluid therapy
[13]. However, it is not without criticism and the definition of appropriate fluid treatment is still open to debate for this group of patients
[14,15].

In this randomized controlled trial, we aim to assess whether the management algorithm using data obtained with a PiCCO system can improve clinical outcomes in critically ill patients with septic shock or ARDS. We hypothesize that a management algorithm based on the PiCCO system will benefit critically ill patients in terms of mortality, length of stay in an ICU and ventilation-free days.

## Methods

The study is designed as a prospective randomized controlled multi-center trial in the ICUs of four tertiary academic centers. These are mixed ICUs treating both surgical and medical patients. The total number of beds is 96. The study will last for a period of 2 years. The end of the study is defined by the last follow-up of the last enrolled patient. The study was approved by the ethics committees of the participating institutions.

### Patient selection

All patients admitted to a participating ICU during the study period will be assessed for potential eligibility. Patients with septic shock, ARDS or both are considered to be eligible. Sepsis is defined as infection plus systemic inflammatory response syndrome (SIRS). General variables are: (1) fever (>38.3°C) or hypothermia (core temperature <36°C); (2) heart rate >90 min^-1^ or >2SD above the normal value for age; (3) tachypnea; (4) altered mental state; (5) significant edema or positive fluid balance (>20 ml.kg^-1^ over 24 hrs); and (6) hyperglycemia (plasma glucose>140 mg.dl^-1^ in the absence of diabetes). Inflammatory variables are: (1) leukocytosis (white blood cell (WBC) count >12000 μL^-1^) or leucopenia (WBC count <4000 μL^-1^); (2) normal WBC count with >10% immature forms; (3) plasma C-reactive protein >2SD above upper normal limit; and (4) plasma procalcitonin >2SD above upper normal limit. Septic shock is defined as a systolic blood pressure (SBP) of <90 mm Hg or mean arterial pressure <70 mm Hg or a SBP decrease >40 mm Hg despite adequate fluid resuscitation
[16]. ARDS is defined according to the Berlin definition
[17]: (1) the onset should be within one week of a known clinical insult or new/worsening respiratory symptoms; (2) chest imaging shows bilateral opacities that cannot be fully explained by effusions, lobar/lung collapse or nodules; (3) respiratory failure is not fully explained by cardiac failure or fluid overload. An objective assessment may be needed to exclude hydrostatic edema if no risk factor is present. ARDS is divided into three mutually exclusive categories of mild (200<PaO_2_/FiO_2_≤300 with positive end-expiratory pressure (PEEP) or continuous positive airway pressure (CPAP)≥5 cmH_2_O), moderate (100<PaO_2_/FiO_2_≤200 with PEEP ≥5 cmH_2_O) and severe (PaO_2_/FiO_2_≤100 with PEEP ≥5 cmH_2_O). The diagnosis of ARDS is made by a specialist. Chest imaging (for example a chest X-ray or computer tomography) is interpreted by a radiologist. Patients are excluded if they met the exclusion criteria: (1) younger than 18 years; (2) experienced hemorrhagic shock; (3) are moribund, or informed consent cannot be obtained; (4) contraindications to catheter insertion, including overlying infection and arterial grafting; (5) conditions likely to render PiCCO measurements inaccurate, including intracardiac shunts, significant tricuspid regurgitation, and cooling or rewarming
[18-20].

### Interventions

#### Experimental intervention

The PiCCO system is used within 2 hours of enrollment. Central venous access is created for the injection of cold water and measurement of central venous pressure (CVP). The choice of type of central venous catheter (CVC) and insertion site are at the discretion of the treating physician. The preferred insertion site is the jugular or subclavian position. We choose the femoral position only when both of these sites are contraindicated. A thermistor-tipped arterial catheter is inserted into the femoral artery. Occasionally, the axillary artery is used when femoral artery catheterization is contraindicated
[21]. Then 15 to 20 ml of normal saline at a temperature <8°C is injected into the central vein, and various hemodynamic parameters can be obtained through analysis of variations in blood temperature taken by the temperature sensor of the arterial catheter. At least three cold boluses are required for each calibration to obtain an acceptable precision
[22]. The calibration should be performed at least every 8 hours, or following a major change in a patient’s clinical condition
[23]. To exclude variations in blood volume and temperature caused by continuous renal replacement therapy (CRRT), the calibration will not be performed immediately after CRRT is switched on or off, and the measurement can be performed after the blood temperature reaches a steady state (after two minutes)
[24,25].

Fluid management aims to optimize the effective circulating blood volume; vasoactive agents are used to achieve a mean arterial pressure of at least 60 mmHg when the volume status is optimal and extravascular lung water is optimized to a negative fluid balance
[26,27]. If the intrathoracic blood volume index (ITBVI) is less than 850 ml.m^-2^, a 500 ml bolus of hydroxyethyl starch 130/0.4 (Voluven®) is infused over 30 min aiming for an ITBVI of 850 to 1000 ml.m^-2^. The bolus can be repeated if the target is not reached. If the ITBVI exceeds 1000 ml.m^-2^, nitroglycerin and/or dobutamine are used based on mean arterial pressure (MAP) and cardiac output (CI). If EVLWI ≥10 ml/kg, furosemide is used. If MAP < 60 mmHg, norepinephrine is started at 0.05 μg.kg^-1^.min^-1^ with the option to increase at an increment of 0.05 μg.kg^-1^.min^-1^. If MAP > 100 mmHg, nitroglycerin is given at the dose range of 0.5 to 3.0 μg.kg^-1^.min^-1^. A red blood cell (RBC) transfusion is triggered when the hemoglobin level Hb <7 g.dl^-1^, and if CI<2.5L.min^-1^.m^-2^ dobutamine is started at the dose of 2.5 μg.kg^-1^.min^-1^. The target is to maintain central venous oxygen saturation ScvO_2_>70% (Figure
1). Dynamic parameters for fluid responsiveness such as pulse pressure variation and stroke volume variation were not included in the protocol due to the requirement for positive ventilation, heavy sedation or paralysis, and a regular cardiac rhythm. The PiCCO system will be removed if the patient is clinically stable for 48 hours as determined by attending physicians. This system can be maintained for a maximum of 10 days. If catheter-related bloodstream infection (CRBSI) is suspected, the central venous catheter will be removed and sent for microbiological study, and the catheter will be exchanged for a new one.

**Figure 1 F1:**
[figure not shown]
**Algorithm for hemodynamic management according to transpulmonary thermodilution-derived data.** If ITBVI < 850 ml.m^-2^, a 500 ml bolus of hydroxyethyl starch 130/0.4 (Voluven®) was infused over 30 min aiming at an ITBVI of 850 to 1000 ml.m^-2^. The bolus can be repeated if the target is not reached. If ITBVI >1000 ml.m^-2^, nitroglycerin and/or dobutamine are used based on MAP and CI. If EVLWI ≥10 ml/kg, furosemide is used. If MAP < 60 mmHg, norepinephrine is started at 0.05 μg.kg^-1^.min^-1^ with the option to increase at an increment of 0.05 μg.kg^-1^.min^-1^. If MAP > 100 mmHg, nitroglycerin is given at the dose range of 0.5 to 3.0 μg.kg^-1^.min^-1^. RBC transfusion is triggered when Hb <7 g.dl^-1^, and if CI <2.5L.min^-1^.m^-2^ dobutamine is started at the dose of 2.5 μg.kg^-1^.min^-1^. The target is to maintain ScvO_2_>70%. CI, cardiac output; EVLWI, extravascular lung water index; Hb, hemoglobin level; ITBVI, intrathoracic blood volume index; MAP, mean arterial pressure; RBC, red blood cell; ScvO_2_, central venous oxygen saturation.

#### Control intervention

Patients in the control arm will not receive PiCCO monitoring, but a central venous catheter is routinely inserted. If the CVP is less than 8 mmHg, a 500 ml bolus of hydroxyethyl starch 130/0.4 (Voluven®) is infused over 30 min aiming to give a CVP of 8 to 12 mmHg. The bolus can be repeated if the target is not reached. If the CVP exceeds 12 mmHg, furosemide and/or nitroglycerin and/or dobutamine are used at the discretion of the attending physician. If MAP is less than 60 mmHg, norepinephrine is started at 0.05 μg.kg^-1^.min^-1^ with the option to increase at an increment of 0.05 μg.kg^-1^.min^-1^. If MAP > 100 mmHg, nitroglycerin is given at the dose range of 0.5 to 3.0 μg.kg^-1^.min^-1^. An RBC transfusion is triggered when Hb<7 g.dl^-1^. ScvO_2_ is maintained >70% (Figure
2).

**Figure 2 F2:**
[figure not shown]
**Algorithm for hemodynamic management in the control arm.** If CVP< 8 mmHg, a 500 ml bolus of hydroxyethyl starch 130/0.4 (Voluven®) was infused over 30 min aiming at a CVP of 8 to 12 mmHg. The bolus can be repeated if the target is not reached. If CVP >12 mmHg, furosemide and/or nitroglycerin and/or dobutamine are used at the discretion of the attending physician. If MAP < 60 mmHg, norepinephrine is started at 0.05 μg.kg^-1^.min^-1^ with the option to increase at an increment of 0.05 μg.kg^-1^.min^-1^. If MAP > 100 mmHg, nitroglycerin is given at the dose range of 0.5 to 3.0 μg.kg^-1^.min^-1^. An RBC transfusion is triggered when Hb<7 g.dl^-1^. ScvO_2_ is maintained >70%. CVP, central venous pressure; Hb, hemoglobin; RBC, red blood cell; ScvO_2_, central venous oxygen saturation.

#### Study end point

The primary endpoint is 30-day mortality (death from any cause before day 30).

#### Secondary outcome measures

ICU length of stay: Since the time of ICU discharge may be affected by the availability of beds on a general ward, we predefine the ICU length of stay as the day from ICU admission to the day when the patient is ready for ICU discharge. A patient is considered ready for discharge when he or she is no longer in need for vital organ support.

Days on mechanical ventilation: The criteria for termination of mechanical ventilation: a cooperative patient, recovery from primary disease, hemodynamically stable, adequate and strong cough reflex, positive end-expiratory pressure <5 cmH_2_O, pressure support <10 cmH_2_O and the spontaneous breathing trial is successfully passed.

Ventilator-free days during 30-day period.

Days of vasoactive agent support: The sum of the number of days with one or more vasoactive agents to maintain a mean arterial pressure >60 mmHg.

Vasoactive-agent-free days in 30-day period.

ICU-free survival days during 30-day period.

Maximum sequential organ failure assessment (SOFA) score during the first 7 days.

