#### Sample size and statistical analysis

We assumed that the overall mortality at 30 days is 40%
[28,29]. A sample size was calculated to detect a 10% difference in mortality at day 30 between the two groups with a two-tailed test, a significance level of 5% and a power of 80%. We plan to include a total of 708 subjects.

Baseline characteristics will be reported. The difference in 30-day mortality between the two groups will be tested using a chi-square test and intention-to-treat (ITT) analysis. Time-to-event variables including length of stay in the ICU, duration of mechanical ventilation and 30-day survival are compared between the two groups using a log-rank test. Multivariate analysis (the Cox proportional hazards regression model) is used to estimate the hazard ratio adjusted for age, severity of illness and disease category. Age and the APACHE II score will be managed as continuous variables. Adverse events will be reported according to the ITT protocol. All tests are two sided and *P*<0.05 is considered to be statistically significant. Statistical analysis will be performed using Stata 11.0 (College Station, TX 77845, USA).

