#### Randomization

Eligible consecutive patients will be randomly assigned to one of the treatment groups using randomization sequences generated by computer and stratified according to the primary diagnostic category on admission, namely, septic shock and ARDS. Allocation concealment is achieved using sequentially numbered, sealed opaque envelopes.

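### ICU length of stay is counted from ICU admission rather than randomisation, so ICU days before randomisation enter the log-rank comparison as noise and can cost power if the delay varies between patients

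*Protocol article*

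**What the plan says.** Under Secondary outcome measures the protocol article fixes both ends of the ICU stay: "we predefine the ICU length of stay as the day from ICU admission to the day when the patient is ready for ICU discharge". Readiness, not actual departure, ends the stay, because the authors want to remove the influence of ward bed availability.

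Under Sample size and statistical analysis the stay is put to a log-rank test as a time-to-event variable: "Time-to-event variables including length of stay in the ICU, duration of mechanical ventilation and 30-day survival are compared between the two groups using a log-rank".

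Three other sections bear on when treatment starts relative to admission:

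- Patient selection: "All patients admitted to a participating ICU during the study period will be assessed for potential eligibility". No limit on the time from admission to randomisation is given.
- Experimental intervention: "The PiCCO system is used within 2 hours of enrollment". The intervention is tied to enrolment, not to ICU admission.
- Randomization: the sequence is "stratified according to the primary diagnostic category on admission, namely, septic shock and ARDS". Time already spent in the ICU is not a stratification factor.

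The Background names length of ICU stay in the hypothesis, beside mortality and ventilation-free days.

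**The concern.** Either qualifying condition can arise after the patient is already in the ICU. The ARDS definition allows onset up to a week after an insult, and septic shock requires hypotension that persists after fluids. Written consent must also come first. Admission and randomisation can therefore be separated by an interval that differs between patients.

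A patient randomised on ICU day d cannot have been discharged before day d, yet a log-rank test timed from admission counts that patient as at risk during those days. It also places in one risk set patients who are at different times since treatment began. If the interval varies, the contrast between arms is diluted.

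At stake is sensitivity on a secondary outcome that the hypothesis names. The article refines the end of the stay to remove noise unrelated to treatment, but leaves such noise in at the start.

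**Working it through.** **1. The article's own figure.** The only sample size stated is for 30-day mortality. Inputs from Sample size and statistical analysis: 40% mortality, a 10-point difference, two-sided 5%, power 80%. The allocation ratio is not given; 1:1 is assumed. Reading the difference as 40% against 30%, with unpooled variance:

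n per arm = (1.960 + 0.842)² × (0.40 × 0.60 + 0.30 × 0.70) / 0.10² = 7.849 × 0.45 / 0.01 = 353.2, so 354 per arm and 2 × 354 = 708.

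This matches "We plan to include a total of 708 subjects" exactly. It does not involve ICU stay, for which the article states neither power nor effect size.

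**2. What the admission clock adds.** Write stay from admission as D + T, where D is ICU time before randomisation and T is time from randomisation to readiness for discharge. D is settled before allocation, so its distribution is the same in both arms:

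- The expected difference in mean days between arms is unchanged.
- If D is the same constant for everyone, the ordering of stays is unchanged, and so is the log-rank statistic.
- If D varies, the ordering is disturbed by something unrelated to treatment.

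**3. Assumed effect.** A discharge hazard ratio of 1.235 was chosen to give about 80% power with 708 discharges: ln(1.235) × √(708/4) − 1.960 = 0.2111 × 13.30 − 1.960 = 0.848, which corresponds to power 0.80. With about one third of stays censored, 1.30 was used.

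**4. Simulation.** All of the following are assumptions: 354 per arm, control-arm scale 10 days, exponential (shape 1) or Weibull shape 1.5 stays, whole days, 4,000 trials per scenario. Power from randomisation was 78.3% to 81.9%. The standard error of one power estimate is √(0.8 × 0.2 / 4000) = 0.6 points. Differences between clocks are more precise, because the same simulated stays are used for both. Change in power, in points, from moving the clock to admission:

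| Delay D | Shape 1, no censoring | Shape 1, censored | Shape 1.5, no censoring | Shape 1.5, censored |
|---|---|---|---|---|
| Constant 2 days | 0.0 | 0.0 | 0.0 | 0.0 |
| Uniform 0–1 day | +0.2 | +0.1 | −0.2 | −0.2 |
| Exponential, mean 0.5 | −0.6 | 0.0 | −0.2 | −0.2 |
| Exponential, mean 1 | −0.8 | −0.7 | −1.3 | −1.3 |
| Exponential, mean 2 | −1.6 | −2.6 | −4.5 | −5.5 |
| Exponential, mean 3 | −4.0 | −5.7 | −10.2 | −12.2 |
| Exponential, mean 5 | −10.4 | −14.1 | −25.7 | −27.2 |

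**5. Spread, not mean, drives the loss.** For an exponential delay the standard deviation equals the mean, so the table does not separate the two. In a further scenario (2,000 trials, no censoring), 80% of patients have no delay and 20% have an exponential delay with mean 7 days. The overall mean is 0.2 × 7 = 1.4 days, and the standard deviation is √(0.2 × 2 × 7² − 1.4²) = √17.64 = 4.2 days. Power falls from 80.0% to 72.0% (shape 1) and from 80.4% to 59.3% (shape 1.5). A late-randomised minority can therefore matter even when most patients are enrolled at admission.

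**6. Type I error.** With no treatment effect (2,000 trials per scenario), the admission clock rejected in 4.45% to 5.95% of trials. The standard error is √(0.05 × 0.95 / 2000) = 0.5 points. There is no sign of inflation.

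**The case against.** The strongest reply is that the harm depends on a quantity the documents never give. A constant delay costs nothing, and delays within about a day cost about a point or less. Stratifying consecutive eligible patients by diagnosis on admission suggests that many are eligible on arrival. Stay distribution, hazard ratio and delay are all assumed, and the simulation represents deaths only as censoring of about a third of stays, although the article expects 40% mortality at 30 days. Admission to readiness is also a coherent measure of total ICU use.

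Most of this stands. A reader might infer that the log-rank test certainly loses power; the documents do not support that without a delay figure. A reader might also infer bias from counting patients as at risk before randomisation. Randomisation makes that time alike in both arms, so it adds noise only.

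The objection does not remove the definition itself. The starting point is stated explicitly, so it is not a detail left out of a condensed article. Enrolment near admission is suggested but not required. The total-use measure can be kept as a descriptive table.

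**Conclusion.** The point holds in a limited form. ICU length of stay, as defined and tested, includes any ICU days before randomisation, which the intervention cannot affect. Under the assumptions above, with exponential delays, the power loss is about 1 point or less for a mean delay of up to 1 day, about 2 to 5 points at 2 days (1.6 to 5.5 across the four scenarios), 4 to 12 at 3 days and 10 to 27 at 5 days. It is zero if the delay is the same for all, and it grows with the spread of the delay. Which case applies cannot be told from the article.

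The comparison stays valid under the null. The 30-day mortality test and the 708 patients are untouched. A reader might extend the point to the ventilator-free, vasoactive-agent-free and ICU-free days or to the 30-day window. The article states no starting point for these, and a condensed article may leave that to the full protocol, so it supports no such finding.

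**What to change.** Define ICU length of stay as the time from randomisation to readiness for ICU discharge, keeping the existing readiness rule, and use that time in the log-rank test. Report ICU days before randomisation by arm as a baseline characteristic, and tabulate total ICU stay from admission descriptively.

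This changes one definition and adds two table rows. It needs the dates of ICU admission and randomisation; the article does not say that both are recorded, but neither should be hard to obtain. It recovers power if delays vary and loses essentially nothing if they do not. Eligibility, treatment and sample size stay as they are. Because the article reports that recruitment is under way, the change should be dated and made before outcomes are compared between arms.
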